### Statistical analysis

Data will be analyzed using the Statistical Package for the Social Sciences (SPSS) version 20. Statistical significance will be accepted when a *p* value is less than 0.05. The intention-to-treat (ITT) principle will be adopted in all analyses. All participants randomized to a group will remain in the group regardless of protocol violations or dropout. Last observation carried forward (LOCF) will be used to impute missing values. Per-protocol analyses will also be conducted. All participants from the ITT population without serious protocol violations will be included in the per-protocol population. Serious violations include exceptions to eligibility criteria and deviations from the treatment scheme such as not completing at least eight of the total of 12 sessions.

For the primary outcome analysis, the change between T0 and T1 in gait speed at a comfortable pace under single-task conditions will be analyzed using Student’s *t* test. Generalized estimating equation (GEE) models will be employed to identify differential changes of secondary outcome measures across multiple time points.

Functional connectivity in the whole brain area will be analyzed using the primary motor cortex as a seed region. Pearson’s correlation coefficient will be used to calculate functional connectivity. Comparisons of functional connectivity will be conducted using two sample *t* tests for between-group differences and paired *t* tests for within-group effects.

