## Methods

### Trial design

This is a prospective, single-blind (assessors), single-center, randomized controlled trial. Eligible participants will be randomly allocated to: 1) a RAGT group or 2) a treadmill training group. Figure 1 shows the Consolidated Standards of Reporting Trials (CONSORT) flow diagram for this study. Baseline assessments (T0) will be conducted to acquire clinical characteristics and values of the primary and secondary outcome measures before the intervention. Postintervention assessments (T1) to compare the immediate efficacy between the two groups will be performed within 3 days after the intervention. Follow-up assessments (T2) will be conducted 1 month after the intervention. All procedures have been approved by the Institutional Review Board of the Seoul National University Hospital in accordance with good clinical practices, the Helsinki Declaration, and national regulations. The clinical trial was also approved by the Korean Ministry of Food and Drug Safety.

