### Sample size

The primary outcome measure in this study is gait speed in postintervention assessments measured by the 10-m walk test (10MWT) at a comfortable pace under single-task conditions. Previous studies, in which similar populations and intervention protocols were employed, have reported that the minimal detectable change in comfortable gait speed measured by the 10MWT was 0.18 m/s [27] and the standard deviation was 0.08–0.20 m/s [13, 17]. Based on those findings, we consider 0.18 m/s as a clinically significant improvement in gait speed and 0.20 m/s as an acceptable standard deviation. Consequently, 20 participants per group will be required to achieve 80% power with a two-tailed α of 0.05, as determined by [28]:$$ N=\frac{2{SD}^2{\left({Z}_{\alpha }+{Z}_{\beta}\right)}^2}{\triangle^2} $$

With an expected drop-out rate of 10%, a total of 44 participants should be recruited, 22 for each group, to establish the relative efficacy of each intervention in improving gait velocity.

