The participants are contacted by phone and mobile text message 1 day before each session to improve adherence. During the clinical trial, participants are prohibited from changing the regimen of dopaminergic medication but they are permitted to keep the previous rehabilitation therapy that was already received. The participation can be discontinued due to the occurrence of serious adverse events or at the participant’s request. Fidelity of the intervention will be assessed through documenting the number and duration of sessions and the minimal and maximal velocity of each session delivered.

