### Data collection, management, and dissemination

Demographic data including age, sex, height, duration of disease, Hoehn-Yahr stage, MMSE score, and comorbidities will be obtained. Outcome measures at T0, T1, and T2 will be acquired as well. All data will be de-identified using an identification number to provide confidentiality and will be collected on paper case report forms and password-protected digital files. Paper case report forms and digital files will be stored in a locked cabinet in a locked office and on a password-protected computer in a locked office, respectively. An independent clinical research assistant will verify the data by review of medical records once a month to guarantee data quality including completeness and accuracy. Any adverse events, any untoward medical occurrence associated with the intervention of this study, will be recorded and reported to the Institutional Review Board and Korean Ministry of Food and Drug Safety (KMFDS). Additional medical procedures will be provided depending on the event. Trial management may be audited by the KMFDS which is independent of investigators at any time.

All authors will have access to the final dataset. Upon completion, trial results will be reported to the funders and submitted to peer-reviewed journals to communicate to participants, healthcare professionals, and the public. Authorship will follow guidelines recommended by the International Committee of Medical Journal Editors (ICMJE). Professional writers will not be employed.

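### LOCF scores every participant missing T1 as zero change, which biases the primary gait-speed comparison even when data are missing completely at random

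*Protocol article*

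**What the plan says.** The Statistical analysis section adopts intention to treat throughout: "All participants randomized to a group will remain in the group regardless of protocol violations or dropout". Gaps are filled by one rule, with no limit by outcome or visit: "Last observation carried forward (LOCF) will be used to impute missing values". For the primary outcome, "the change between T0 and T1 in gait speed at a comfortable pace under single-task conditions will be analyzed" with Student's t test. For the rest, "Generalized estimating equation (GEE) models will be employed to identify differential changes of secondary outcome measures across multiple time points".

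The section on data collection gives three measurement times: "Outcome measures at T0, T1, and T2 will be acquired as well". Trial design places the last of them: "Follow-up assessments (T2) will be conducted 1 month after the intervention".

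Missing data are expected. The Sample size section says: "With an expected drop-out rate of 10%, a total of 44 participants should be recruited, 22 for each group". The Interventions section adds: "The participation can be discontinued due to the occurrence of serious adverse events", or at the participant's own request.

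The only other analysis named is per-protocol. It selects on eligibility and on completing at least eight of the 12 sessions, so it does not test the missing-data rule.

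**The concern.** LOCF needs a relevant earlier value to carry. For the primary endpoint the only earlier value is the pre-training baseline. The rule therefore assumes that nobody who misses T1 changed at all, and it analyses that assumption as if it were a measurement. If both arms improve, as the trial expects of two active training programmes, each missing T1 pulls its own arm's mean toward zero.

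Losses spread evenly over the arms shrink the difference. Uneven losses push it in a direction set by the arm that loses more, so LOCF cannot be defended as conservative: losses from the comparator favour RAGT. Uneven loss is possible here. The Discussion says that patients and therapists cannot be blinded, and the treadmill arm follows the robot's velocity schedule without the robot. The documents give no dropout rate by arm.

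The protocol itself fixes the rule, so this is not a detail left to an unseen analysis plan.

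**Working it through.** **Inputs from the protocol.** Difference 0.18 m/s, SD 0.20 m/s, two-sided alpha 0.05, power 80%, 20 evaluable and 22 recruited per arm, 10% dropout (Sample size); visits T0, T1 and T2; ITT, LOCF and t test (Statistical analysis).

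**Assumptions.** 0.20 is the SD of the change. The mean change in the treadmill arm (μC), the split of dropouts by arm and missingness completely at random are not in the documents. Completely random loss is used because an observed-case analysis is then unbiased, so any bias comes from LOCF alone.

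**1. The plan's own figure.** n = 2 × 0.20² × (1.96 + 0.8416)² / 0.18² = 0.08 × 7.849 / 0.0324 = 19.38, rounded up to 20 per arm. Then 19.38 / 0.9 = 21.5, rounded up to 22, or 44 in total. The plan's figures reproduce. A t test on 20 completers per arm has 79.2% power, which is the fair comparator below.

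**2. Formula.** With k of n participants in an arm missing T1, the LOCF mean change is μ(n − k)/n. The bias in the RAGT minus treadmill difference is μC·kC/n − μR·kR/n.

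**3. True difference 0.18 m/s.** Expected dropouts are 10% of 44 = 4.4, so about 4. At exactly 10% per arm the estimate is 0.9 × 0.18 = 0.162. With whole patients it is as follows (power from simulating the planned t test, 200,000 replicates).

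| Missing T1, RAGT / treadmill | μC | Expected LOCF difference (m/s) | LOCF power |
|---|---|---|---|
| 2 / 2 | 0 | 0.18 × 20/22 = 0.164 | 79% |
| 2 / 2 | 0.10 | 0.164 | 77% |
| 2 / 2 | 0.18 | 0.164 | 74% |
| 4 / 0 | 0.10 | 0.28 × 18/22 − 0.10 = 0.129 | 53% |
| 4 / 0 | 0.18 | 0.36 × 18/22 − 0.18 = 0.115 | 39% |
| 0 / 4 | 0.10 | 0.28 − 0.10 × 18/22 = 0.198 | 92% |
| 0 / 4 | 0.18 | 0.36 − 0.18 × 18/22 = 0.213 | 94% |

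Observed cases give 0.180 m/s and about 79% power in every row. In the two 4 / 0 rows, coverage of the true 0.18 by the LOCF 95% interval falls to 89% and 86%.

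**4. No true difference, all four missing in the treadmill arm.** The spurious difference in favour of RAGT is (common gain) × 4/22.

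| Common gain (m/s) | Spurious difference (m/s) | Type I error |
|---|---|---|
| 0.10 | 0.018 | 5.9% |
| 0.18 | 0.033 | 7.9% |
| 0.30 | 0.055 | 12.0% |

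With two missing per arm, type I error does not exceed 5% (4.7%, 4.0% and 2.9%).

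**5. T2.** Let the true effects be δ1 at T1 and δ2 at T2, with a fraction d of each arm missing T2. If all of them attended T1, LOCF estimates (1 − d)δ2 + dδ1, which is too large if the effect fades and too small if it grows. If all of them left before T1, it estimates (1 − d)δ2, which is always shrunk. The direction is not fixed.

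**The case against.** At the planned dropout, split evenly, the harm is modest: 0.016-0.018 m/s toward zero, a loss of at most about 5 points of power against 79%, and no excess of false positives. The larger figures need all four losses in one arm and a comparator gain that the documents do not give. In special cases there is no bias, for example when the treadmill arm does not change and only that arm loses patients. All of this stands. It limits the size of the point but does not justify a rule whose error depends on who happens to drop out.

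The alternative is not free of assumptions either. A participant with only T0 adds little to a mixed model, so the result lies close to an observed-case analysis under missing at random. That assumption is doubtful after serious adverse events. This also stands, and it is why the fix includes a sensitivity analysis.

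Three stronger readings are tempting and are not supported:

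- **Understated error.** A reader might infer that filled-in values make the standard error too small. In 100,000 simulated trials with 10% random dropout per arm, the true spread of the LOCF estimate and its mean reported standard error were 0.0586 and 0.0580 (0.18 against 0), and 0.0603 and 0.0599 (0.28 against 0.10). LOCF's standard error is usually below the observed-case 0.063, but it matches the estimator's own variability. The fault is bias.
- **Overstated persistence at T2.** Step 5 shows that the bias can go either way. The article also describes no T2 analysis of gait speed: the longitudinal models are stated for secondary outcomes.
- **Cancelled assessments.** The Interventions sentence says that participation can be discontinued. It does not say that T1 and T2 are then omitted. It is an ambiguity worth closing.

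**Conclusion.** The point holds for the primary analysis. LOCF turns each missing T1 into a zero change and biases the arm difference even under completely random loss. At the plan's own 10%, split evenly, a true 0.18 m/s becomes about 0.162-0.164, with power of about 74-79% against 79% for observed cases. With all four expected losses in one arm, the estimate can fall to 0.115-0.129 (RAGT losses, treadmill gain 0.18 or 0.10), or type I error can reach about 6%, 8% or 12% (treadmill losses, common gain 0.10, 0.18 or 0.30).

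These sizes rest on a change SD of 0.20, 22 per arm and the assumed gains and splits. For secondary outcomes at T2, LOCF assumes no change after the last visit attended; that bias has no fixed direction, and the documents give no basis for a figure.

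**What to change.** Before unblinding, change the Statistical analysis section as follows:

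1. Make the primary analysis a likelihood-based repeated-measures model on the observed T1 and T2 gait speeds, with baseline, arm, time and arm-by-time, and report the T1 contrast. Multiple imputation by arm is an acceptable alternative.
2. Do not fill the secondary GEE or other longitudinal models by LOCF. GEE can use the observed visits as they are, which is valid if data are missing completely at random.
3. Keep LOCF only as a sensitivity analysis, and add one for departures from missing at random.
4. State that participants who stop training but have not withdrawn consent are still measured at the scheduled T1 and T2. This is a data-collection rule and leaves decisions about treatment untouched.

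The cost is small: new wording, a little more analysis work (the MIXED procedure in SPSS fits the model) and attendance at visits already planned. The article reports that recruitment is ongoing and that analysts are blinded until the analysis, so the change can be made credibly. The price is reliance on missing at random, which item 3 examines.

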### Outcome measures

The primary outcome measure is gait speed measured by the 10MWT at a comfortable pace under single-task conditions [29]. The 10MWT is a common measure to evaluate gait velocity and highly reliable for assessing gait speed in patients with PD [29].

The secondary outcomes include dual-task interference [30], the Berg Balance Scale (BBS) [31], Timed Up and Go (TUG) test [32], the Korean version of the Falls Efficacy Scale-International (KFES-I) [33, 34], the New Freezing of Gait Questionnaire (NFOG-Q) [35], and the Movement Disorder Society-sponsored revision of the Unified Parkinson’s Disease Rating Scale (MDS-UPDRS) [36].

Dual-task interference, an indicator of gait automaticity, is defined by the difference between dual- and single-task performance [37]. To evaluate dual-task performance, cognitive dual-task walking [38] will be measured while performing the Wechsler Forward Digit Span [39], and physical dual-task walking will be measured while carrying a tray with two cups of water [40, 41]. The BBS measures balance function during sitting, standing, and changing positions. It consists of 14 items and the total score ranges from 0 to 56 [42]. The tool is clinically valid in PD patients [31]. The TUG test is a reliable measure for mobility in the elderly. During the test, patients stand up from a chair, walk for 3 m, turn, walk back, and sit down. It is also a highly reliable tool to assess mobility in PD [32]. KFES-I is a valid method to assess fear of falling in the elderly [33]. It is a self-reported measure of concerns about falls during activities of daily living. It consists of 16 items scored on a four-point scale [34]. NFOG-Q is a freezing of gait (FOG) questionnaire which assesses FOG severity and gait disturbances. It is a reliable tool to measure the FOG and the functional impact in patients with PD [35]. MDS-UPDRS, a clinical rating scale for PD, contains four parts [36]. A total of 50 questions rate disability or impairment on a scale of 0–4.

The 10MWT, BBS, and TUG test will be assessed by a physical therapist and the MDS-UPDRS will be administered by a licensed clinician. All assessors will be blinded to group assignment. Figure 3 shows the schedule for outcome measures evaluated at each visit.

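### The primary t test on change is valid but usually less precise than adjusting for baseline gait speed, and the endpoint wording and the SD of 0.20 m/s need to be made definite

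*Protocol article*

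**What the plan says.** The protocol article describes the primary endpoint in three places.

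- The Sample size section has: "The primary outcome measure in this study is gait speed in postintervention assessments measured by the 10-m walk test (10MWT) at a comfortable pace". This is a level at one visit.
- The Outcome measures section has: "The primary outcome measure is gait speed measured by the 10MWT at a comfortable pace under single-task conditions". Neither a visit nor a change is named.
- The Statistical analysis section has: "the change between T0 and T1 in gait speed at a comfortable pace under single-task conditions will be analyzed using". The test it names is Student's t test. This is a change score, compared between groups without a covariate.

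The planning values are given as "we consider 0.18 m/s as a clinically significant improvement in gait speed and 0.20 m/s as an acceptable standard deviation", after a report that in earlier studies "the standard deviation was 0.08–0.20 m/s". Neither sentence says whether the SD is that of gait speed at a visit or of its change. No T0-T1 correlation is given.

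Baseline speed will be available for adjustment. The data collection section says "Outcome measures at T0, T1, and T2 will be acquired as well". Randomization is 1:1 in blocks of 4 and 6, and stratification by gait speed is not mentioned.

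**The concern.** T0 gait speed is likely to be among the best predictors of T1 gait speed, and it is measured before allocation. Subtracting it, as a change score does, amounts to fixing its regression slope at 1. When T0 and T1 have equal variances the best slope is r, the T0-T1 correlation. A fixed slope of 1 then adds noise unless r is close to 1. It also leaves the change score correlated with baseline, so a chance difference in starting speed between the arms carries through to the observed result.

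At stake is precision in a trial planned on 20 evaluable participants per group, where the planned test has little power to spare. The loose wording adds to this. The power of the change test depends on whether 0.20 m/s describes a level or a change, and the article leaves that open.

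**Working it through.** **Inputs from the Sample size section.** Difference 0.18 m/s, SD 0.20 m/s, two-sided alpha 0.05, power 80%, 20 evaluable per group, 22 per group recruited.

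**Assumptions, not in the article.** Equal variances at T0 and T1, a linear relation between them, and a range of values for r.

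**1. The plan's own figure.** n = 2 × 0.20² × (1.960 + 0.842)² / 0.18² = 19.38, rounded up to 20 per group; 20 × 1.10 = 22, or 44 in total. This reproduces. Calculated exactly with the noncentral t distribution, power at 20 per group is 79.2%.

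**2. Variances.** With s the SD of gait speed at a visit:

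- Change score: 2s²(1 − r)
- Adjusted for T0: s²(1 − r²)
- Ratio, adjusted to change: (1 + r)/2. This is 0.75, 0.85, 0.90 and 0.95 at r = 0.5, 0.7, 0.8 and 0.9.

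**3. Cost of the covariate at 20 per group.** Degrees of freedom fall from 38 to 37, and the variance is multiplied by about 1 + 1/36 = 1.028. At r = 0.95 the net variance ratio is 0.975 × 1.028 = 1.002, so the gain is gone.

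**4. Power if 0.20 m/s is the SD of change.** The adjusted SD is 0.20 × √((1 + r)/2).

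| r | Adjusted SD (m/s) | t test on change | Adjusted for T0 |
|---|---|---|---|
| 0.5 | 0.173 | 79.2% | 88.4% |
| 0.7 | 0.184 | 79.2% | 84.3% |
| 0.8 | 0.190 | 79.2% | 82.2% |
| 0.9 | 0.195 | 79.2% | 80.1% |
| 0.95 | 0.198 | 79.2% | 79.1% |

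**5. Power if 0.20 m/s is the SD of T1 speed.** The change SD is 0.20 × √(2(1 − r)) and the adjusted SD is 0.20 × √(1 − r²).

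| r | Change SD (m/s) | Adjusted SD (m/s) | t test on change | Adjusted for T0 |
|---|---|---|---|---|
| 0.3 | 0.237 | 0.191 | 65.0% | 81.7% |
| 0.5 | 0.200 | 0.173 | 79.2% | 88.4% |
| 0.7 | 0.155 | 0.143 | 94.7% | 96.9% |

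On this reading an unadjusted comparison of T1 speed has 79.2% power, so below r = 0.5 the change score does worse than ignoring baseline altogether.

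**6. Simulation check.** In 20,000 simulated trials per setting with 20 per group, type I error lay between 4.7% and 5.1% for both methods. At r = 0.5 simulated power was 78.9% for change and 88.2% adjusted, in line with the tables.

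**7. Chance imbalance.** If the SD of T0 speed is 0.20 m/s, the standard error of the baseline difference is 0.20 × √(2/20) = 0.063 m/s. A difference of 0.05 m/s is therefore unremarkable. It shifts the change-score estimate by (1 − r) × 0.05, in the direction opposite to the imbalance: 0.025 m/s at r = 0.5, 0.010 at r = 0.8 and 0.005 at r = 0.9. Against the target of 0.18 m/s these are about 14%, 6% and 3%.

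**8. Level or change as outcome.** Since change = T1 − T0, regressing change on group and T0 instead of T1 on group and T0 lowers the T0 coefficient by 1 and alters nothing else. The group estimate, its standard error and its p value are identical.

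**The case against.** The strongest reply is that nothing in the planned test is wrong. One outcome, one interval and one test are fixed. Under 1:1 randomization the t test on change is unbiased over randomizations and holds its error rate. This stands. A reader might infer that regression to the mean biases the trial. The shift in step 7 is conditional on a particular baseline difference, and the t test's standard error already covers that variability.

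The gain may also be small. The article calls the 10-m walk test highly reliable. If its minimal detectable change of 0.18 m/s is read as 1.96 × √2 × SEM (an assumption), the SEM is 0.065 m/s and reliability is 1 − 0.065²/0.20², or about 0.89. With the lower SD of 0.08 m/s the same reading gives 0.34. Reliability is also not the T0-T1 correlation after four weeks of training. So a high r is plausible but not established, and at r = 0.9 adjustment adds about one power point.

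A reader might further infer two conflicting primary endpoints. The documents do not go that far. The Sample size section also speaks of an improvement, and the primary objective concerns greater improvement. Under randomization the expected group difference is the same for T1 speed and for change. The mismatch is largely one of wording; what remains open is which quantity the SD describes.

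Finally, a reader might infer that T2 gait speed has no planned analysis, because "Generalized estimating equation (GEE) models will be employed to identify differential changes of secondary outcome measures across multiple time points". A condensed article commonly leaves the follow-up analysis of the primary measure to the full protocol or analysis plan, so this is not counted as a fault.

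**Conclusion.** The point holds as a matter of efficiency and clarity, not of validity. The plan fixes an unadjusted t test on change although T0 speed is collected, and adjusting for T0 speed is more precise unless r is about 0.95 or higher. At 20 per group the gain runs from about 9 power points at r = 0.5 to about 1 at r = 0.9 if 0.20 m/s is the SD of change. If it is the SD of T1 speed, the gain is about 17 points at r = 0.3 and about 2 at r = 0.7.

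These figures rest on assumed values of r and on equal T0 and T1 variances. It would be too strong to say that adjustment is free, always better, or a cure for chance imbalance in general. It spends a degree of freedom and about 2.8% in variance, and it deals with imbalance in baseline gait speed only, under a linear model. Nor does it by itself settle the wording of the endpoint or the meaning of 0.20 m/s; those need a sentence each.

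**What to change.** - Make the primary analysis a linear model of T1 comfortable single-task gait speed on group and T0 gait speed, and report the adjusted group difference with its confidence interval.
- Keep the Student's t test on the T0-T1 change as a sensitivity analysis.
- Use one wording of the primary endpoint, including the visit, in the Sample size, Outcome measures and Statistical analysis sections.
- State whether 0.20 m/s is the SD of T1 speed or of change.

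The cost is a few sentences, one degree of freedom and about 2.8% in variance at 40 evaluable participants. No new data are needed and N = 44 is unchanged. The article describes recruitment as ongoing and the analysts as blinded until statistical analysis, so the change can be dated and made before anyone sees results by group. If a joint model of T1 and T2 is preferred, it should not be treated as interchangeable with the T1 model. With missing data the two can differ, and the joint model would have to be reconciled with the plan's last-observation-carried-forward rule.

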### Randomization and blinding

Randomization and allocation will be performed using computer-generated block randomization with a block size of 4 and 6. An independent researcher who is not in contact with any patient will perform the randomized allocation. The ratio between the RAGT and treadmill training groups will be 1:1. Details of the allocated group will be given in sequentially numbered, opaque, sealed envelopes to the research assistants in sequential order. The principal investigator, outcome assessors, and data analysts will be blinded to the group allocations of the participants until statistical analysis.

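### GEE with 20 to 22 participants per arm and no stated small-sample allowance: with an uncorrected robust variance, the clinical secondary tests run at about 6% to 7.5%, not 5%

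*Protocol article*

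**What the plan says.** The Statistical analysis section assigns one method to the secondary outcomes over time: "Generalized estimating equation (GEE) models will be employed to identify differential changes of secondary outcome measures across multiple time points". The criterion for every analysis is the same: "Statistical significance will be accepted when a *p* value is less than 0.05". It does not name the variance estimator, the working correlation, the reference distribution or a small-sample correction.

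The number of clusters follows from the Sample size section: "20 participants per group will be required to achieve 80% power with a two-tailed α of 0.05", and then "With an expected drop-out rate of 10%, a total of 44 participants should be recruited, 22 for each group". Allocation is equal: "The ratio between the RAGT and treadmill training groups will be 1:1". Each participant contributes three visits: "Outcome measures at T0, T1, and T2 will be acquired as well".

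The Outcome measures section lists six clinical secondary outcomes: dual-task interference, BBS, TUG, KFES-I, NFOG-Q and MDS-UPDRS. The abstract adds functional connectivity, but the Statistical analysis section compares that by two-sample and paired t tests. The primary outcome, change in gait speed from T0 to T1, is also compared by a t test.

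**The concern.** GEE in its ordinary form is a large-sample method. The robust variance is built from squared residuals, which are too small because the means have been fitted to the same data. The Wald statistic is then referred to a chi-square or normal distribution, as if the variance were known. Both simplifications are harmless with hundreds of clusters. With 40 to 44 they push in the same direction: p values too small and intervals too narrow.

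The plan thus treats one small sample in two ways. The primary t test allows for the limited degrees of freedom, while nothing is said about such an allowance for the clinical secondary outcomes. At stake is whether those results hold the 5% level that the article sets. One of them, dual-task interference, also carries the mechanistic aim in the Background.

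**Working it through.** **Inputs from the article.** n = 20 evaluable or 22 randomised per arm, 1:1 allocation, three visits, two-sided α = 0.05. Because missing values are carried forward, the intention-to-treat GEE can include all 22 per arm.

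**Assumptions not in the article.** Identity link, time as a categorical factor with all group-by-time means free, complete balanced records, equal covariance in the two arms, and normal errors for the exact results.

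**The plan's own figure.** "we consider 0.18 m/s as a clinically significant improvement in gait speed and 0.20 m/s as an acceptable standard deviation". The stated formula gives N = 2 × 0.20² × (1.960 + 0.842)² / 0.18² = 19.4, so 20 per arm. Then 20 × 1.10 = 22 per arm and 44 in total. The stated sample size is reproduced. It rests on the primary outcome alone, and no operating characteristic is given for the GEE tests.

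**Size of the uncorrected robust test.** In this balanced design the sandwich variance of a between-arm difference in change equals (n − 1)/n times the unbiased variance.

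- Single contrast: size = P(|t with 2n − 2 df| > 1.960 × √((n − 1)/n)).
  - n = 20: 1.960 × √(19/20) = 1.910 on 38 df, size 6.4%.
  - n = 22: 1.960 × √(21/22) = 1.915 on 42 df, size 6.2%.
- 2-df group-by-time test: size = P(F(2, 2n − 3) > 5.991 × ((n − 1)/n) × (2n − 3)/(2(2n − 2))).
  - n = 20: 5.991 × 0.950 × 37/76 = 2.771 on (2, 37) df, size 7.6%.
  - n = 22: 5.991 × 0.9545 × 41/84 = 2.791 on (2, 41) df, size 7.3%.

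These results do not depend on the within-person correlation. At 18 per arm, as might arise in a per-protocol set, they are 6.5% and 7.9%.

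**Intervals.** Width relative to a t-based interval is 1.910/2.024 = 0.944 at n = 20 and 1.915/2.018 = 0.949 at n = 22, so about 6% and 5% too narrow. Coverage of a nominal 95% interval is 93.6% and 93.8%.

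**Simulation.**

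| Setting | Single contrast | 2-df test |
|---|---|---|
| n = 20, normal errors, correlation 0.5 or 0.8 | 6.3% | 7.4% to 7.6% |
| n = 22, normal errors, correlation 0.5 or 0.8 | 6.2% | 7.3% |
| n = 20, skewed errors | 6.3% | 7.2% |
| n = 20, fitted GEE, robust variance, 1,500 trials | 5.6% | 7.8% |
| n = 22, fitted GEE, robust variance, 1,500 trials | 5.5% | 6.9% |

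The last two rows carry a Monte Carlo error of about 0.6 percentage points and agree with the formulas.

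**After correction, n = 20.**

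- Kauermann-Carroll scaling multiplies the sandwich by n/(n − 1), which removes the bias here. With a t or F reference the size is 5.0% (1 df) and 4.9% to 5.0% (2 df).
- Mancl-DeRouen multiplies it by (n/(n − 1))². With the chi-square reference kept, the size is about 5.1% and 5.8%. With a t reference, a single contrast has size P(|t with 38 df| > 2.024 × √(20/19) = 2.077) = 4.5%, slightly conservative.

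**The case against.** The strongest reply is that the article never says an uncorrected sandwich variance will be used. Taking its absence of detail as a choice would attribute to the plan something it does not contain. The estimator is a detail that a condensed article may leave to a full protocol or analysis plan, and GEE as named is compatible with correct size. In the fitted-GEE check at n = 20, an exchangeable working correlation with model-based variance gave 4.7% and 5.3%. This stands, and it makes the point conditional. It does not remove it: the method in its usual robust form does not hold the stated level at the stated n. The model-based alternative also needs a suitable working correlation. With an independence structure and model-based variance, the same check rejected in none of 1,500 trials.

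Three stronger readings are tempting and are not supported.

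- A reader might infer that every secondary test is affected. Functional connectivity is tested by t tests, so it is not.
- A reader might add that GEE on observed data needs data missing completely at random. The article carries the last observation forward, so that is not the analysis planned.
- A reader might count the six outcomes as part of this problem. That is multiplicity, which a corrected variance would not address.

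The size also needs proportion. An excess of about half the nominal rate arises only for the 2-df test at 20 per arm. With 22 per arm and a single contrast the excess is 1.2 percentage points, and the article does not say which of the two tests will be reported.

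**Conclusion.** The point holds in conditional form, for the six clinical secondary outcomes only. With an uncorrected robust variance and a chi-square reference, the excess over 5% is 1.2 to 1.4 percentage points for a single contrast and 2.3 to 2.6 points for the group-by-time test. The figures rest on balanced complete data, free group-by-time means and an identity link; skewed errors changed them little. The article does not show that this variance will be used, so a reader should not conclude that the planned tests are certain to exceed 5%. The trial's main conclusion is not touched. This is a modest weakness that is cheap to remove.

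**What to change.** Add one sentence to the analysis plan before the data are analysed. Either of these would do:

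- Keep GEE and specify a small-sample corrected covariance, such as Kauermann-Carroll or Mancl-DeRouen, with a t or F reference. The reference matters: Mancl-DeRouen with chi-square still leaves the 2-df test at about 5.8%.
- Replace GEE by a linear mixed model for repeated measures with Satterthwaite or Kenward-Roger degrees of freedom. This adds distributional assumptions, which deserve thought for bounded scores such as the BBS, and it is not required to solve the problem.

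In either case, state the working correlation or covariance structure, and whether the reported test is the 2-df group-by-time test or named single contrasts.

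No extra participants or data are needed. Intervals become slightly wider: at n = 20 an unbiased t-based interval is 1/0.944 = 1.06 times the uncorrected one. Whether the named software version offers these corrections cannot be judged from the article and should be checked.
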